## Abstract

**Background:**

Differentiation of Parkinson’s disease (PD) from the various types of atypical parkinsonism (AP) such as multiple system atrophy (MSA), progressive supranuclear palsy (PSP), dementia with Lewy bodies (DLB), corticobasal syndrome (CBS) and vascular parkinsonism (VP), can be challenging, especially early in the disease course when symptoms overlap. A major unmet need in the diagnostic workup of these disorders is a diagnostic tool that differentiates the various disorders, preferably in the earliest disease stages when the clinical presentation is similar. Many diagnostic tests have been evaluated, but their added value was studied mostly in retrospective case-control studies that included patients with a straightforward clinical diagnosis. Here, we describe the design of a prospective cohort study in patients with parkinsonism in an early disease stage who have an uncertain clinical diagnosis. Our aim is to evaluate the diagnostic accuracy of (1) detailed clinical examination by a movement disorder specialist, (2) magnetic resonance imaging (MRI) techniques and (3) cerebrospinal fluid (CSF) biomarkers.

**Methods/design:**

Patients with parkinsonism with an uncertain clinical diagnosis and a disease course less than three years will be recruited. Patients will undergo extensive neurological examination, brain MRI including conventional and advanced sequences, and a lumbar puncture. The diagnosis (including level of certainty) will be defined by a movement disorders expert, neuroradiologist and neurochemist based on clinical data, MRI results and CSF results, respectively. The clinical diagnosis after three years’ follow-up will serve as the “gold standard” reference diagnosis, based on consensus criteria and as established by two movement disorder specialists (blinded to the test results). Diagnostic accuracy of individual instruments and added value of brain MRI and CSF analysis *after* evaluation by a movement disorder expert will be calculated, expressed as the change in percentage of individuals that are correctly diagnosed with PD or AP.

**Discussion:**

This study will yield new insights into the diagnostic value of clinical evaluation by a movement disorder specialist, brain MRI and CSF analysis in discriminating PD from AP in early disease stages. The outcome has the potential to help clinicians in choosing the optimal diagnostic strategy for patients with an uncertain clinical diagnosis.

**Trial registration:**

NCT01249768, registered November 26 2010.

**Electronic supplementary material:**

The online version of this article (10.1186/s12883-018-1072-x) contains supplementary material, which is available to authorized users.

## Background

Differentiation between Parkinson’s Disease (PD) and the various forms of atypical parkinsonism (AP) can be difficult, especially early in the disease course. This is due to overlap in clinical symptoms, certainly when the clinical picture has not yet developed fully. Forms of AP such as multiple system atrophy (MSA), progressive supranuclear palsy (PSP) or corticobasal syndrome (CBS) follow a more malignant disease course than PD and, unlike PD, generally do not respond well to dopaminergic therapy.

While difficult, a correct diagnosis is important for adequate disease management and patient counseling, as well as for research purposes. If, in the future, any disease-modifying therapy becomes available, then reliable diagnostic tools will be essential to distinguish PD from AP at the earliest possible stage.

Because there is not yet a reliable objective test for PD and AP, expert opinion remains the gold standard for the clinical diagnosis. In the hands of a movement disorders specialist, the diagnostic accuracy is higher (90%) compared to judgment by a general neurologist (76%) [1, 2]. Although the clinical diagnosis after several years of follow-up correlates highly with the neuropathological diagnosis upon post-mortem examination, the diagnostic accuracy of the initial diagnosis varies greatly, and can be as low as 30% [1, 3–5]. When a clinician has little doubt about the diagnosis, ancillary investigations have hardly any diagnostic value. But when the clinical picture is puzzling, which is often the case early in the disease course, reliable biomarkers are needed for accurate and early differentiation between PD and AP.

Brain MRI is nowadays part of the diagnostic workup of patients with suspected parkinsonism, mainly to exclude secondary causes of parkinsonism (e.g. tumor, hydrocephalus, multiple sclerosis, vascular parkinsonism). Conventional MRI can demonstrate abnormalities characteristic for various AP syndromes, such as putaminal or olivopontocerebellar atrophy in MSA, midbrain atrophy in PSP and asymmetric regional cortical atrophy in CBS.

Due to limited sensitivity of these MRI abnormalities (e.g. 68% for cerebellar atrophy and 59% for putaminal atrophy), their contribution to the clinically based diagnosis is limited [6]. These abnormalities often occur late in the disease course, which make them of less diagnostic value in early disease stages. However, advances in neuroimaging techniques are promising to provide new biomarkers for improved differentiation between the different parkinsonian syndromes.

Magnetic resonance volumetry (MRV), diffusion tensor imaging (DTI), susceptibility weighted imaging (SWI) and resting state functional magnetic resonance imaging (rs-fMRI) are examples of new MR techniques which have become available [7–10]. However, these new techniques are often difficult to interpret for the individual patient, since MRI patterns are investigated on a group level. Moreover, validated diagnostic criteria are generally lacking. For example, DTI studies found alterations in fractional anisotropy and mean diffusivity in the substantia nigra in PD patients and in the cerebellum, pons, cerebellar peduncles and putamen in MSA patients. Furthermore, increased iron accumulation in the substantia nigra on SWI sequences is suggestive for PD as is increased putaminal hypointensity for MSA [7, 11, 12]. Rs-fMRI has been applied to assess functional abnormalities in neural networks of PD patients. Several studies identified PD-specific network patterns compared to healthy controls, but if these patterns differ from AP cases is yet unknown [13].

Furthermore, research on cerebrospinal fluid (CSF) biomarkers has strongly developed over the past decade. Analysis of brain specific proteins in CSF can be of value in distinguishing PD from AP. In PD patients, concentrations of brain specific proteins and neurotransmitter metabolites are generally within normal ranges, whereas in AP aberrant levels of these proteins and metabolites can be found. Currently, neurofilament light chain (NFL), total and phosphorylated tau (t-tau and p-tau), α-synuclein (α-syn) and amyloid-β42 (Aβ42) seem to be the most promising biomarkers for the differential diagnosis of parkinsonian syndromes. NFL levels are increased in AP compared with PD and healthy controls, tau proteins are elevated in CBS, while Aβ42 and tau are associated with cognitive decline (dementia) in PD and DLB [14–21].

Given the complexity of parkinsonian syndromes it is likely that neither a single clinical test nor a single biomarker can differentiate between the different parkinsonian syndromes. A combination of parameters could however improve diagnostic accuracy [14, 15, 18, 19, 21]. On the other hand, MRI is time-consuming and expensive, CSF analysis requires a lumbar puncture and many centers lack a neurologist with experience in movement disorders. More knowledge about the diagnostic value of each test could help clinicians in selecting the best available test.

With this prospective cohort study, we aim to gain insight in which single or combined ancillary investigation (including the opinion of a movement disorder specialist) will have the highest diagnostic yield for discrimination of PD and AP in early disease stage when diagnostic uncertainty is high.

## Methods/design

### Study design

A prospective observational cohort study to assess the diagnostic value of clinical evaluation by a movement disorder specialist, brain MRI and CSF analysis in discriminating different forms of parkinsonism early in the disease course. The Medical Ethics Committee Arnhem-Nijmegen approved the study. Written informed consent will be obtained from all patients after detailed explanation of the procedures.

### Objectives

The main objective of our study is to determine the diagnostic accuracy of detailed clinical examination by a movement disorder specialist, conventional and advanced brain MRI techniques and CSF analysis to differentiate PD from AP in clinically uncertain cases. Secondary objective is to identify potential variables for differentiation between PD and AP.

Third objective is to identify potential discriminative variables between the various forms of AP.

### Study population

Patients will be recruited from our outpatient movement disorder clinic and outpatient neurology clinics of referring general hospitals. Inclusion criteria are clinical signs and symptoms of parkinsonism (hypokinetic-rigid syndrome) with uncertain clinical diagnosis and disease duration less than three years. Exclusion criteria are age below 18 years and unstable co-morbidity. Inclusion and exclusion criteria are provided in Table 1.

**Table 1 Tab1:** Inclusion and exclusion criteria

Inclusion criteria	Exclusion criteria
Hypokinetic-rigid syndrome of neurodegenerative origin Disease duration < 3 years Age > 18 years	Instable comorbidity Incompetent patient A medical history of brain surgery Other neurodegenerative disorder Diagnosis of *clinically established* or *probable* PD Diagnosis of *probable* MSA, PSP, CBS or VP
	*Exclusion criteria for MRI:* Claustrophobia Metal devices Unable to lie still for 30 min Pregnancy
	*Exclusion criteria for lumbar puncture:* Coagulation disorders Oral anticoagulants

*PD* Parkinson’s disease, *MSA* multiple system atrophy, *PSP* progressive supranuclear palsy, *CBS* corticobasal syndrome, *VP* vascular parkinsonism

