### Ancillary investigations

#### MRI

All patients will have a brain MRI at first presentation performed on 3 Tesla MRI scanner (Siemens Magnetom Trio, Erlangen, Germany) by a standardized scanning protocol. Conventional MRI sequences will include 3D T1 MPrage, T2 turbo-spin echo, T2 fluid attenuated inversed recovery (FLAIR), and proton density sequences. Advanced MRI sequences will include diffusion weighted imaging (DWI) and diffusion tensor imaging (DTI), SWI and rs-fMRI. All MRI scans will be evaluated in a systematic fashion by two neuroradiologists blinded for clinical symptoms and outcome. The presence of the following abnormalities on conventional MRI sequences will be scored using a diagnostic workstation (Agfa-Impax version 6.5.3, Gevaert, Mortsel, Belgium): atrophy and T2 hypo-intensity of the putamen, putaminal rim sign, frontal lobe and parietal lobe atrophy, lateral, third and fourth ventricle dilatation, midbrain and pontine atrophy, hummingbird sign, atrophy of the cerebellum and cerebellar vermis, atrophy of the medulla oblongata, T2 hyper-intense signal changes of the middle cerebral peduncle and hot cross bun sign, dilated perivascular spaces, lacunar infarctions and white matter changes. Advanced imaging sequences will be analyzed by dedicated software packages, including ‘Functional MR Imaging of the Brain Software Library‘(FSL, University of Oxford, United Kingdom) and ‘Statistical Parametric Mapping’ (SPM, Trust Centre of Neuroimaging, London, United Kingdom).

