### Assessment of diagnoses

Before inclusion, the referring neurologist will be asked to establish the probable diagnosis based on routine clinical examination. Specifically, a level of diagnostic (un) certainty will be indicated on a scale of 0–100. After inclusion, a movement disorder expert will also be asked for the diagnosis and level of certainty based on the clinical evaluation; a neuroradiologist makes the diagnosis based on imaging findings and a neurochemist based on CSF analysis.

The final clinical diagnosis will be established after three years of follow-up in consensus by two independent neurologists specialized in movement disorders, and this will serve as the “silver standard” reference diagnosis. This reference diagnosis will be based on the clinical data at baseline, the disease course after 3 years follow-up and with adherence to the following international clinical criteria: Movement Disorder Society clinical diagnostic criteria for PD [35], Gilman criteria for MSA [36], the movement disorder society criteria for PSP [37]**,** Armstrong criteria for CBS [38] and Zijlmans criteria for vascular parkinsonism [39]**.** These neurologists will be blinded for the results of the ancillary investigations, except for the conventional MRI because this is part of routine procedures in clinical practice. See Fig. 1 for a flowchart of the study design.

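### Table 1's cause-based entry criterion conflicts with the running text and with vascular parkinsonism as a target diagnosis, and could let routine MRI, an index test, shape who is enrolled

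*Protocol article*

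**What the plan says.** Eligibility is described in three places in the protocol article.

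- Table 1, inclusion column: "Hypokinetic-rigid syndrome of neurodegenerative origin", with limits on disease duration and age. Diagnostic uncertainty enters through the exclusion column, which removes patients who already have a sufficiently firm diagnosis, including "Diagnosis of *probable* MSA, PSP, CBS or VP".
- Study population, running text: "Inclusion criteria are clinical signs and symptoms of parkinsonism (hypokinetic-rigid syndrome) with uncertain clinical diagnosis and disease duration less than three years". It then refers the reader to Table 1.
- Abstract: "Patients with parkinsonism with an uncertain clinical diagnosis and a disease course less than three years will be recruited".

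Three other sections bear on how the Table 1 line would be applied.

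- Background: "Brain MRI is nowadays part of the diagnostic workup of patients with suspected parkinsonism, mainly to exclude secondary causes of parkinsonism". It gives four examples of such causes, and VP is one of them.
- MRI: "All patients will have a brain MRI at first presentation performed on 3 Tesla MRI scanner".
- Assessment of diagnoses: "Before inclusion, the referring neurologist will be asked to establish the probable diagnosis based on routine clinical examination". The same section gives criteria for a reference diagnosis of VP and describes conventional MRI as part of ordinary practice.

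The opening of the abstract names VP among the forms of AP that are to be told apart from PD.

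**The concern.** Table 1 sets a condition on the cause of the syndrome. The text and abstract set one only on uncertainty and duration. Because the text defers to the table, the stricter line governs, and it does not fit the study's own list of target diagnoses.

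The condition is also hard to apply without leaning on an index test. These patients are recruited because their diagnosis is unclear, so whether the cause is neurodegenerative rests on judgement or on a test. If that test is a routine MRI, patients with vascular changes on the scan may be judged ineligible. VP counts as AP, so these would be AP cases that MRI is able to recognise. Losing them would lower the apparent sensitivity of MRI for AP and its added value after the specialist's assessment, relative to CSF. The Discussion promises the general neurologist a comparison of specialist, MRI and CSF, and that comparison depends on which patients were let in.

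**Working it through.** The plan attaches no figure to this point, so the main check is a comparison of passages.

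**Step 1: is there a difference in the entry criteria?** Yes. Table 1 restricts by origin; the running text and the abstract do not. All three limit disease duration to under three years. The text and abstract state uncertainty directly, and Table 1 achieves it through its exclusions.

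**Step 2: does the origin line fit the handling of VP?**

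| Place | Status of VP |
|---|---|
| Abstract, background paragraph | A form of AP |
| Background section | A secondary cause that MRI is used to exclude |
| Table 1, inclusion | Barred, if a secondary cause is not neurodegenerative |
| Table 1, exclusion | Barred only when probable, so a less certain case may enter |
| Assessment of diagnoses | Has its own reference criteria, so is an expected final diagnosis |

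Rows 1, 4 and 5 treat VP as part of the study. Rows 2 and 3 together put it outside. They cannot all be followed.

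**Step 3: could MRI influence entry?** The article names one tool for excluding secondary causes, brain MRI, and calls conventional MRI routine. A scan before referral is therefore possible. The Objectives make conventional MRI an index test. Nothing in the article says whether an earlier scan may be used to judge the origin line.

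**Step 4: direction and possible size.** Let *v* be the VP share of AP, *Se_d* the MRI sensitivity in degenerative AP and *Se_v* that in VP. Then

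Se(all AP) = (1 − v) × Se_d + v × Se_v,

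and if every VP case is screened out beforehand, the loss in measured sensitivity is v × (Se_v − Se_d).

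The document supplies only stand-ins for *Se_d*: the Background's 59% (putaminal atrophy) and 68% (cerebellar atrophy). These describe single signs and not a full radiological reading. The values of *v* (0 to 20%) and *Se_v* (80 to 100%) are assumptions.

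- v = 0: loss 0.
- v = 0.05, Se_v = 0.80: 0.05 × (0.80 − 0.59) = 0.0105; 0.05 × (0.80 − 0.68) = 0.006. About 1 point.
- v = 0.20, Se_v = 1.00: 0.20 × (1.00 − 0.59) = 0.082, that is 67.2% falling to 59%; 0.20 × (1.00 − 0.68) = 0.064, that is 74.4% falling to 68%.

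The range is 0 to about 8 percentage points. It shows direction and order of magnitude only.

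**The case against.** The strongest reply is that the running text is a summary. It defers to Table 1 and omits several other criteria, so it is not a rival rule. The pre-inclusion diagnosis rests on clinical examination, the study MRI is given to all patients, and no passage makes any scan an eligibility step. The question is PD against AP, so keeping out tumour or hydrocephalus does not bias the accuracy of MRI for that question.

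Most of this stands, and it rules out four stronger readings.

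- A reader might infer that the article says neurodegenerative origin is established mainly by MRI. It says what routine MRI is mainly used for, which is a different statement.
- A reader might infer that MRI selects the study population by design. The article allows that possibility but does not prescribe it.
- A reader might infer that patients found later to have another cause are deleted, which would inflate accuracy. No passage provides for such removal, and the handling of these patients may be set out in the full protocol or analysis plan.
- A reader might infer that different sites would enrol different populations. Patients come from several clinics, but all are examined by a movement disorder specialist at one centre.

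The reply does not answer the VP conflict. Deferring to Table 1 makes it sharper, because Table 1's inclusion line and its exclusion line then disagree about less-than-probable VP. Nor does it say how the origin line is to be judged when the diagnosis is uncertain.

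**Conclusion.** The point holds as a conflict in the eligibility wording with a plausible route to selection bias. Table 1 adds a condition on cause that the text and abstract lack, and that condition does not fit VP's place among the target diagnoses. Because cause is unsettled at entry, and MRI is at once the named means of excluding secondary causes, part of routine care and an index test, applying the line may remove AP cases that MRI would detect.

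The size is not derivable from the document. The 0 to about 8 points of MRI sensitivity rest on assumed VP shares, assumed MRI sensitivity in VP, single-sign sensitivities as stand-ins, and removal of every VP case. The correction is worth making because it is cheap and has to be settled before the results can be interpreted.

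**What to change.** 1. Reconcile the Table 1 line with the running text, for example by asking for a hypokinetic-rigid syndrome whose clinical diagnosis is uncertain, with no reference to origin. State explicitly whether VP that is less than probable is eligible.
2. State that no enrolled patient is excluded or removed because of the study MRI, the study CSF result or the final diagnosis.
3. Report how many patients have a reference diagnosis that is neither PD nor AP, with the call each test made for them. Keep sensitivity and specificity in the PD/AP subset.
4. Record whether a diagnostic MRI was available before referral. This does not undo selection by an earlier scan, but it lets a reader see how far it could have operated.

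The cost is a change of wording, one recorded field and one extra table. The downside is that a few patients who are neither PD nor AP stay in the reported cohort, so the percentage correctly diagnosed may look slightly less favourable.

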### Clinical examination

#### Evaluation by a movement disorder specialist

All patients will be interviewed and examined by a movement disorder specialist at the outpatient neurology department of the Radboud university medical center in Nijmegen (The Netherlands).

#### Structured interview

Standardized questionnaires on demographics, medical history, cardiovascular risk factors, activities in daily living, medication use, disease onset, clinical signs, most affected body site, balance and fear of falling will be administered at baseline and every year during follow-up for 3 years. In addition, the Non-Motor Symptom Scale (NMSS) [22], Hospital Anxiety and Depression Scale (HADS), Questionnaire for Impulsive-Compulsive Disorders in Parkinson’s Disease (QUIP) and Epworth Sleepiness Scale (ESS) will be scored [23–25]. A translated version of the structured questionnaires are provided as Additional file 1 with this article.

#### Cognitive assessment

A measurement of global cognitive function will be assessed by the Mini Mental State Examination (MMSE) [26], Frontal Assessment Battery (FAB) [27] and Cambridge Neuropsychological Automated Test Battery [28] at baseline and after three years follow-up.

#### Neurological examination

Standard neurological examination will be performed including testing of cranial nerves, motor and sensory function, tendon reflexes and presence or absence of primary reflexes. Horizontal and vertical blood pressure will be measured to screen for orthostatic hypotension.

In addition, the following clinimetric scales will be assessed: Unified Parkinson’s Disease rating scale (UPDRS) III and IV, Hoehn and Yahr disease severity score [29] and Scale for the assessment and rating of ataxia (SARA) [30]. The neurological examination will be performed and videotaped at baseline and after three years follow-up.

### Ancillary investigations

#### MRI

All patients will have a brain MRI at first presentation performed on 3 Tesla MRI scanner (Siemens Magnetom Trio, Erlangen, Germany) by a standardized scanning protocol. Conventional MRI sequences will include 3D T1 MPrage, T2 turbo-spin echo, T2 fluid attenuated inversed recovery (FLAIR), and proton density sequences. Advanced MRI sequences will include diffusion weighted imaging (DWI) and diffusion tensor imaging (DTI), SWI and rs-fMRI. All MRI scans will be evaluated in a systematic fashion by two neuroradiologists blinded for clinical symptoms and outcome. The presence of the following abnormalities on conventional MRI sequences will be scored using a diagnostic workstation (Agfa-Impax version 6.5.3, Gevaert, Mortsel, Belgium): atrophy and T2 hypo-intensity of the putamen, putaminal rim sign, frontal lobe and parietal lobe atrophy, lateral, third and fourth ventricle dilatation, midbrain and pontine atrophy, hummingbird sign, atrophy of the cerebellum and cerebellar vermis, atrophy of the medulla oblongata, T2 hyper-intense signal changes of the middle cerebral peduncle and hot cross bun sign, dilated perivascular spaces, lacunar infarctions and white matter changes. Advanced imaging sequences will be analyzed by dedicated software packages, including ‘Functional MR Imaging of the Brain Software Library‘(FSL, University of Oxford, United Kingdom) and ‘Statistical Parametric Mapping’ (SPM, Trust Centre of Neuroimaging, London, United Kingdom).

